# 2 STUDY DESIGN & OBJECTIVES

The open-label study is designed as a pilot prospective, randomized controlled trial to assess the impact of the YouScript® Personalized Prescribing System on decreased re-hospitalizations, ED visits, falls, and improvement in select OASIS metrics and clinical decision-making. The decision to utilize the YouScript® Personalized Prescribing System and all treatment decisions will be made in accordance with usual care practice, and will be made prior to the decision to participate in the study.

Outcomes will be compared between a group of prospectively enrolled patients undergoing CYP2D6, CYP2C19, CYP2C9, VKORC1, CYP3A4, and CYP3A5 testing with the YouScript® Personalized Prescribing System at the discretion of their clinician (i.e. “tested” patients) and a group of similar patients at home health meeting the same enrollment criteria (excluding the YouScript® testing) and matched on key characteristics to the tested patients using propensity score matching.

The study aims to initially enroll 100 patients from a single home health agency in the United States. The study includes 2 study arms.

| Arm | Sample size | Treatment | Treatment |
|-----|-------------|-----------|-----------|
|-----|-------------|-----------|-----------|

|              |    |            |                                                               |
|--------------|----|------------|---------------------------------------------------------------|
| Intervention | 50 | Tested     | YouScript®                                                    |
| Controls     | 50 | Not tested | Treatment as usual (i.e. standard drug information resources) |

## 2.1 Primary objective

To assess the impact of pharmacogenetic testing and YouScript® Personalized Prescribing System on these outcomes at 30 and 60 days post discharge:

- The number of re-hospitalizations
- The number of Emergency Department visits

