## PROTOCOL SUMMARY

**Title:** A Pilot Prospective, Randomized Controlled Trial Assessing the Clinical Impact of Integrated Pharmacogenetic Testing on Selected OASIS Metrics, Re-hospitalizations and Emergency Department visits

**Synopsis:** Patients meeting eligibility criteria will be randomized into two groups, one receiving pharmacogenetic testing and the other not receiving pharmacogenetic testing. In this open-label trial, a pharmacist will make medication therapy recommendations using YouScript® Personalized Prescribing System for patients who receive genetic testing and standard drug information resources per usual for patients who do not undergo pharmacogenetic testing.

Both groups will be followed for 60 days. The number of re-hospitalizations and emergency department (ED) visits will be recorded as well as time to first re-hospitalization and time to first ED visit. Select OASIS metrics (e.g. M1034, M1242, M1710, M1720, M1745, M2110) and depression using PHQ-2 will be evaluated and documented at time of admission to home health, at 30 days, and at 60 days for improvement in overall status, pain, confusion, anxiety, depression, disruptive behavior, and the need for assistance with activities of daily living (ADLs) and instrumental activities of daily living (IADLs). The number of falls will be collected as well as the proportion of YouScript® recommendations accepted by study pharmacist and passed on to clinicians and the proportion of recommendations accepted by clinicians.

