**Objectives:**

Primary:

- To assess the number of re-hospitalizations at 30 and 60 days post discharge with pharmacogenetic testing and YouScript® Personalized Prescribing System
- To assess the number of Emergency Department visits at 30 and 60 days post discharge with pharmacogenetic testing and YouScript® Personalized Prescribing system

Exploratory:

- To assess time to first re-hospitalization.
- To assess time to first Emergency Department visit.
- To assess the impact of genetic testing on overall status according to OASIS M1034 at 30 and 60 days post discharge.
- To assess the impact of genetic testing on frequency of pain according to OASIS M1242 at 30 and 60 days post discharge.
- To assess the impact of genetic testing on frequency of confusion according to OASIS M1710 at 30 and 60 days post discharge.
- To assess the impact of genetic testing on frequency of anxiety

according to OASIS M1720 at 30 and 60 days post discharge.

- To assess the impact of genetic testing on depression according to PHQ-2 at 30 and 60 days post discharge.
- To assess the impact of genetic testing on frequency of disruptive behavior according to OASIS M1745 at 30 and 60 days post discharge.
- To assess the impact of genetic testing on the frequency of ADL and IADL assistance according to OASIS M2110 at 30 and 60 days post discharge.
- To assess whether YouScript® testing decreases falls
- To assess the proportion of YouScript® Personalized Prescribing System recommendations accepted by the study pharmacist and passed on to clinicians.
- To assess the proportion of study pharmacist recommendations acted on by clinicians.

**Sample size** 100 patients (50 intervention, 50 controls)

**Population:** The study population consists of patients aged 65 and older who are currently enrolled in home health and are presently taking or initiating treatment with at least one oral form of medication with a significant drug-drug or drug-gene interaction as defined by FDA boxed warning, FDA cautionary labeling, clinical literature or a YouScript® algorithm-predicted significant effect.

Those meeting eligibility criteria will be prospectively enrolled in either the “tested” group and undergo YouScript® testing or “untested” group and not undergo YouScript® testing.

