**Description of Intervention:** Patients in the “tested” group will receive genetic testing. The study pharmacist will review drug-drug, drug-gene, and drug-drug-gene interactions using YouScript® Personalized Prescribing System to provide drug therapy recommendations to prescribers.

**Estimated Time to Complete Enrollment:** Up to 20 weeks (5+ months)

**Subject Participation Duration:** Each patient will be followed for 60 days from date of admission to home health

**Total Study Duration:** Up to 8 months, depending on the rate of accrual

**Figure 1:** Schematic of Study Design.

[figure not shown]

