## **5 DATA MANAGEMENT CONSIDERATIONS**

### **5.1 Outcome measures**

The following outcome measures will be recorded by the nurse upon patient admission, Day 30, and Day 60. PI will extract the data from patient charts and manually enter the data into the data entry form (Appendix C):

| Endpoint              | Indicator   | Scale                                                                                                                                                                                                                                                                                                                                                                                                                                                                                                                                                                                                                                                         |
|-----------------------|-------------|---------------------------------------------------------------------------------------------------------------------------------------------------------------------------------------------------------------------------------------------------------------------------------------------------------------------------------------------------------------------------------------------------------------------------------------------------------------------------------------------------------------------------------------------------------------------------------------------------------------------------------------------------------------|
| Overall status        | OASIS M1034 | 
0 - The patient is stable with no heightened risk(s) for serious complications and death (beyond those typical of the patient's age).
 
1 - The patient is temporarily facing high health risk(s), but is likely to return to being stable without heightened risk(s) for serious complications and death (beyond those typical of the patient's age).
 
2 - The patient is likely to remain in fragile health and have ongoing high risk(s) of serious complications and death
 
3 - The patient has serious progressive conditions that could lead to death within a year.
 
UK - The patient's situation is unknown or unclear.
 |

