## APPENDIX A: SCHEDULE OF PROCEDURES

| Study-Specific Procedures                                                          | Screening | Baseline
(Day 0) | Follow-up
(Day 30) | Follow-up
(Day 60) |
|------------------------------------------------------------------------------------|-----------|---------------------|-----------------------|-----------------------|
| Signed Consent Form                                                                | X         |                     |                       |                       |
| Verification of Eligibility                                                        | X         |                     |                       |                       |
| YouScript® testing                                                                 |           | X                   |                       |                       |
| Assess OASIS M1034/Overall status*                                                 |           |                     | X*                    |                       |
| Assess OASIS M1242/Pain*                                                           |           |                     | X*                    |                       |
| Assess OASIS M1710/Confusion*                                                      |           |                     | X*                    |                       |
| Assess OASIS M1720/Anxiety*                                                        |           |                     | X*                    |                       |
| Assess PHQ-2/Depression*                                                           |           |                     | X*                    |                       |
| Assess OASIS M1745/Disruptive Behavior*                                            |           |                     | X*                    |                       |
| Assess OASIS M2110/Need for ADL & IADL Assistance*                                 |           |                     | X*                    |                       |
| Abstraction of data from patient chart regarding healthcare resource utilization** |           |                     | X                     | X                     |
| Survey of clinician regarding impact on clinical decision-making                   |           |                     | X                     | X                     |

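### The 30- and 60-day windows have contradictory start points, none of them stated to be randomisation, so events before assignment can enter the primary counts and dilute the effect by an amount that depends on an unstated lag

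*Combined protocol and SAP*

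**What the plan says.** Three start points appear for the same windows.

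- **Discharge.** Section 2.1 sets the primary outcomes "on these outcomes at 30 and 60 days post discharge". The Protocol Summary objectives agree ("To assess the number of re-hospitalizations at 30 and 60 days post discharge"), and section 2.2 carries the phrase over to the exploratory outcomes.
- **Home-health admission.** The Protocol Summary states: "Each patient will be followed for 60 days from date of admission to home health". The synopsis places the OASIS and PHQ-2 assessments "at time of admission to home health, at 30 days, and at 60 days". Section 5.1 has the outcome measures "recorded by the nurse upon patient admission, Day 30, and Day 60", and the example data entry form in Appendix C has Admit, Day 30 and Day 60 columns.
- **Baseline (Day 0).** Appendix A puts "YouScript® testing" in this column but does not link Day 0 to discharge, admission, enrolment or randomisation.

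Under section 3.4, arms follow patient numbers given in order of enrolment, from a list made in advance. Assignment therefore takes effect at enrolment. Sections 3.3 to 3.3.2 place enrolment after chart review of new home-health patients and after consent.

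Section 7, its repeat in the SAP extract and the March 2016 amendment name Poisson regression (or negative binomial) for the counts and the log-rank test for times to first event. None gives a time origin.

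**The concern.** The contradiction affects the primary endpoint. Discharge has no definition. Section 3.5 uses the word for leaving home health, and section 3.1 requires no hospital stay, so for some patients a post-discharge window may have no start date at all. Two analysts could follow the protocol faithfully and report different primary counts from the same records.

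Neither named anchor is the moment of assignment. The summary describes the population as "patients aged 65 and older who are currently enrolled in home health", no limit is set on time from admission to enrolment, and nothing tells the analyst to drop earlier events. The intervention cannot have prevented an event that preceded assignment. Counting such events adds the same expected number to each arm and pulls the rate ratio towards 1. The same unstated origin applies to falls, to both time-to-event outcomes and to the composites added after study completion.

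**Working it through.** The documents give no event rate, effect size or power, so there is no figure of the plan's own to reproduce. The check measures how much the choice of origin could matter.

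**Inputs from the documents:** windows T = 30 and 60 days; 50 patients per arm; two-sided 0.05.

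**Assumed, because the documents do not give them:** lag L from the window's start to assignment of 0, 3, 7 or 14 days; true rate ratio 0.60; constant event rate; control mean of 0.25, 0.5 or 1.0 events per patient per 60 days (power only).

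**Dilution.** During the L pre-assignment days both arms have the control rate, so observed RR = (L + (T − L) × 0.60) / T.

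| Lag (days) | T = 60 | T = 30 |
|---|---|---|
| 0 | 0.60 | 0.60 |
| 3 | (3 + 57 × 0.60)/60 = 0.62 | (3 + 27 × 0.60)/30 = 0.64 |
| 7 | (7 + 53 × 0.60)/60 = 0.65 | (7 + 23 × 0.60)/30 = 0.69 |
| 14 | (14 + 46 × 0.60)/60 = 0.69 | (14 + 16 × 0.60)/30 = 0.79 |

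The pre-assignment share of the window is 7/60 = 12% and 7/30 = 23% at 7 days, and 14/60 = 23% and 14/30 = 47% at 14 days.

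**Power.** Wald test on the log rate ratio of two Poisson totals: z = |ln RR| / sqrt(1/E_control + 1/E_tested), power = Φ(z − 1.96) + Φ(−z − 1.96).

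For 0.5 control events per 60 days and T = 60, E_control = 50 × 0.5 = 25.

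- L = 0: E_tested = 25 × 0.60 = 15; z = 0.511/0.327 = 1.56; power 35%.
- L = 7: E_tested = 25 × 0.647 = 16.2; z = 0.436/0.319 = 1.37; power 28%.

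The same steps for every lag at this rate give:

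| Lag (days) | 60-day power | 30-day power |
|---|---|---|
| 0 | 35% | 20% |
| 3 | 32% | 17% |
| 7 | 28% | 13% |
| 14 | 22% | 9% |

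Over control rates of 0.25 to 1.0, moving from no lag to 7 days takes 60-day power from 20–60% to 16–49%, and 30-day power from 12–35% to 9–22%. Overdispersion would lower all of these.

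**If the rate is not constant.** Two departures work in opposite directions.

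- Suppose risk is highest early (assumed half-life 20 days). The share of control-arm events in the first 7 days is (1 − 2^(−7/20)) / (1 − 2^(−T/20)) = 0.333 for T = 30 and 0.246 for T = 60. The observed ratios become 0.333 + 0.667 × 0.60 = 0.73 and 0.246 + 0.754 × 0.60 = 0.70.
- Suppose patients with early events are not enrolled. Pre-assignment time is then partly event-free and dilutes less. In the limit of no such events the ratio stays at 0.60, but at a 7-day lag the time at risk falls to 23 of 30 or 53 of 60 days.

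**The case against.** The strongest reply is that the working text mostly uses one clock. The synopsis, section 5.1 and the data entry form all run from home-health admission. Section 3.3 recruits from new home-health patients, and section 3.3.2 records OASIS and PHQ-2 at enrolment/baseline. On that reading admission, baseline and Day 0 nearly coincide, the post-discharge wording is loose drafting, and with same-day enrolment the dilution is nil. Moreover, this is a pilot that makes no power claim.

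Much of this stands. The lag may be small, and no passage gives one. A reader might infer that admission preceded randomisation by days, or that earlier events were in fact counted; the documents show only that both are possible. They do allow for elapsed time: section 3.3.2 checks that subjects still meet the criteria, and Appendix A separates Screening from Baseline.

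The reply does not remove the conflict. The objectives define the primary endpoint by discharge, and nothing in section 7 or the amendment overrides them. Being a pilot lowers the stakes for power, but it does not make an endpoint with two start dates reproducible.

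One caution about the remedy also stands. The Appendix A footnote makes the baseline and Day 60 OASIS assessments part of standard care, so moving them to a randomisation clock could require extra visits.

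**Conclusion.** The point holds as a contradiction in the start of the primary windows, with a conditional consequence. The stated anchors disagree, neither of the two named anchors is randomisation, Day 0 is undefined, and no rule keeps earlier events out. Following either named anchor as written can count pre-assignment events.

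The consequence is dilution and lost power. With a true ratio of 0.60 and a constant rate, the observed ratio runs from 0.60 (no lag) to 0.69 at 60 days and 0.79 at 30 days (14-day lag). The lag, the rate and the true ratio are all assumptions.

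Two stronger readings are not supported.

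- A reader might infer bias in favour of testing. If both arms use the same anchor, pre-assignment events balance in expectation, and nothing in the documents shows that the anchor differed by arm.
- A reader might infer that the 30-day result mainly measures the period before the study. Under a constant rate even a 14-day lag makes 47% of that window pre-assignment, and no such lag is documented.

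**What to change.** **In the protocol**

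- Define Day 0 as the date of randomisation (enrolment) for the counts of re-hospitalisations, ED visits and falls and for both times to first event. Treat earlier events as baseline history.
- Record the hospital discharge date (where there is one), the home-health admission date and the randomisation date on the data entry form. The example form as reproduced shows none of them.
- Reconcile the Protocol Summary objectives and participation duration, sections 2.1, 2.2 and 5.1, and Appendices A and C.
- Leave OASIS and PHQ-2 on their existing admission, Day 30 and Day 60 schedule, and align the objectives' wording for those outcomes with it.

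The cost is wording and three date fields. The downside is that event follow-up ends later by the enrolment lag.

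**For the completed study**

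- State which origin was used for the counts and times.
- Report the gap from that origin to enrolment by arm.
- Re-run the counts and times to first event from enrolment as a sensitivity analysis, including the composites added in March 2016. Section 5.1 says that re-hospitalisation dates were written on the office board and ED visits in the charts, so this needs a return to source records and not to the derived day counts alone.

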## 2.2 Exploratory:

To assess the impact of pharmacogenetic testing and YouScript® Personalized Prescribing System on these outcomes at 30 and 60 days post discharge:

- Time to first re-hospitalization
- Time to first ED visit
- Overall status according to OASIS M1034
- Frequency of pain according to OASIS M1242
- Frequency of confusion according to OASIS M1710
- Frequency of anxiety according to OASIS M1720
- Depression according to PHQ-2
- Frequency of disruptive behavior according to OASIS M1745
- Frequency of ADL and IADL assistance according to OASIS M2110
- The number of falls (at the end of study)
- Acceptance by the study pharmacist and passing on to clinicians (at the end of study)
- The proportion of study pharmacist recommendations acted on by clinicians (at the end of study)

# 3 STUDY PROCEDURES

## 3.1 Inclusion Criteria

- Age 65 or older.
- Willing and able to provide informed consent for study participation either directly or by a legally authorized representative (LAR).
- Presently taking or beginning treatment with at least one of the following

oral forms of medication (excluding medications taken PRN) (generic name given with major U.S. brand name given in parentheses). These medications are subject to significant drug-gene interactions as defined by FDA boxed warning, FDA cautionary labeling, clinical literature or a YouScript® algorithm-predicted significant effect:

|                              |                         |                                |
|------------------------------|-------------------------|--------------------------------|
| Amitriptyline (Elavil)       | Fluoxetine (Prozac)     | Pimozide (Orap)                |
| Aripiprazole (Abilify)       | Flurbiprofen (Ansaid)   | Piroxicam (Feldene)            |
| Atomoxetine (Strattera)      | Fluvoxamine (Luvox)     | Proguanil [(Malarone (combo))] |
| Carvedilol (Coreg)           | Haloperidol (Haldol)    | Propafenone (Rythmol)          |
| Celecoxib (Celebrex)         | Hydrocodone             | Propranolol (Inderal)          |
| Citalopram (Celexa)          | Ibuprofen (Motrin)      | Risperidone (Risperdal)        |
| Clobazam (Onfi)              | Iloperidone (Fanapt)    | Sertraline (Zoloft)            |
| Clomipramine (Anafranil)     | Imipramine (Tofranil)   | Tetrabenazine (Xenazine)       |
| Clopidogrel (Plavix)         | Indomethacin (Indocin)  | Thioridazine (Mellaril)        |
| Clozapine (Clozaril)         | Meloxicam (Mobic)       | Timolol (Apotimol)             |
| Codeine [Tylenol #3 (combo)] | Metoprolol (Toprol XL)  | Tolterodine (Detrol)           |
| Desipramine (Norpramin)      | Mexiletine (Mexitil)    | Torsemide (Demadex)            |
| Dextromethorphan (Delsym)    | Nortriptyline (Pamelor) | Tramadol (Ultram)              |
| Diazepam (Valium)            | Omeprazole (Prilosec)   | Trimipramine (Surmontil)       |
| Doxepin (Sinequan)           | Oxycodone (Oxycontin)   | Venlafaxine (Effexor)          |
| Escitalopram (Lexapro)       | Paroxetine (Paxil)      | Voriconazole (Vfend)           |
| Esomeprazole (Nexium)        | Perphenazine (Trilafon) | Vortioxetine (Brintellix)      |
| Fesoterodine (Toviaz)        | Phenobarbital (Luminal) | Warfarin (Coumadin)            |
| Flecainide (Tambocor)        | Phenytoin (Dilantin)    |                                |

### 3.2 Exclusion Criteria

Patients meeting any of the following criteria will not be eligible for enrollment/inclusion in the study (ICD9 codes are included in parentheses):

- Previous CYP testing (CPT codes 81225, 81226, 81227, 81355, 81401)
- History of organ transplant (199.2; 238.77; 414.06; 414.07; 996.80-996.89; E878.0; V42.0-V42.7; V42.81-V42.84; V42.89; V42.9; V45.87; V49.83; V58.44)
- Current malabsorption syndrome (579.0), including the following:
  - Intestinal malabsorption (579.8, 579.9)
  - Postoperative malabsorption (579.3)
  - Short bowel syndrome (579.3)
- Treatment of invasive solid tumors or hematologic malignancies in the last year, excluding in situ cancers or non-melanoma skin cancer (basal cell carcinoma)
- End Stage Renal Disease (ESRD)
- Persistent acute renal failure: complete loss of kidney function >4 weeks (requiring dialysis)

- Renal failure by:
  - Glomerular filtration rate (GFR): SCr > 3 times baseline or GFR decreased 75% or SCr ≥4 mg/dL; acute rise ≥0.5 mg/dL
  - OR
  - Urine Output (UO): UO < 0.3 mL/kg/h 24 h (oliguria) or anuria 12 h

